### Trial design {8}

This is a randomized, masked, placebo-controlled superiority trial to evaluate the efficacy of locally administered gentamicin versus placebo in the prevention of fracture-related infection in open tibia fracture patients. Patients will be randomized using randomly permuted blocks in a 1:1 allocation ratio.

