### Sample size {14}

Data from a prior randomized control trial conducted at Open Tibia Trial (MOI) and the FLOW trial was used to estimate the base rate of reoperation at 12% [13, 14]. Previous literature suggests using local aminoglycoside antibiotics provides a relative risk reduction of approximately 50% for FRI [15]. An absolute risk reduction of 12 to 6% with a two-tailed alpha of 0.05, a power of 80%, and an estimated loss to follow-up rate of 20% suggests a sample size of 445 individuals per treatment arm for a total of 890 enrolled patients.

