### Statistical methods used for secondary and additional outcomes

These analyses are designed to provide additional insight and support for the primary analysis and to assess whether the methodological choices we made had an undue effect on the results. In reporting, they will be sharply distinguished from the primary outcome. Additional sensitivity analyses will be conducted based on the following variables as baseline covariates: Gustilo-Anderson fracture type, OTA Open Fracture Classification for contamination, time from injury to first debridement, and method of fixation. We will make available the results of Fisher’s exact test on the 2 × 2 cross-tabulation of the reoperation binary outcome and the treatment assignment. This does not consider the observation time and thus is an independent statistical procedure and may yield different decisions than the primary prespecified analysis. We will also report the 95% confidence interval for the risk difference between the groups. Because this will be conducted by an independent regression (binomial regression with the identity link), these new findings may be statistically inconsistent with the main analysis. Thus, we will only report 95% confidence intervals, omitting *P*-values.

The risk difference is interpretively important and may be useful in future meta-analytic studies. Intent-to-treat analysis is recommended but impossible when the primary outcome is missing. We will conduct exploratory regression of missingness and observation time, using the following predictors when appropriate: gender, severity of injury, cost of travel to clinic, and age.

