### Methods in analysis to handle protocol non-adherence and any statistical methods to handle missing data {20c}

Intent-to-treat analysis will be performed where possible. Missing data in any study outcome will not undergo imputation. We will conduct exploratory regression of missingness and observation time, using the following predictors when appropriate: gender, severity of injury, cost of travel to clinic, and age.

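### The identity-link risk difference has no evident way to use partial follow-up, so with 20% planned loss its value depends modestly on how patients lost without an infection are coded

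*Protocol article*

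**What the plan says.** Under *Statistical methods for primary and secondary outcomes {20a}*, the protocol article analyses FRI as a binary outcome by binomial regression with a complementary log-log link. The reason given is that this lets person-time enter. The estimate is a relative hazard.

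Under *Statistical methods used for secondary and additional outcomes*, it adds a risk difference with a 95% confidence interval from a different model: "Because this will be conducted by an independent regression (binomial regression with the identity link), these new findings may be statistically inconsistent". The inconsistency meant is with the primary result. For that reason no P-value is given, and these analyses are to be kept clearly apart from the primary one. The same section says that the risk difference matters for interpretation and may serve later meta-analyses. It also says: "Intent-to-treat analysis is recommended but impossible when the primary outcome is missing".

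Section {20c} adds: "Missing data in any study outcome will not undergo imputation". The section *Sample size {14}* plans for "an estimated loss to follow-up rate of 20" per cent.

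The risk-difference sentence does not name its outcome. Because the section presents these analyses as support for the primary analysis, I read it as FRI. The argument is the same for any binary outcome followed to 12 months.

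**The concern.** A binomial model with an identity link on a yes/no outcome returns a difference of two proportions. A patient seen free of infection to month 4 and then lost is neither a known yes nor a known no at 12 months. In the primary model that patient contributes the time observed. In the risk-difference model the patient must be coded as a no or left out, because imputation is barred.

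The coding is not symmetric. A patient diagnosed with FRI at month 3 who then leaves has a settled outcome. Keeping that patient while dropping those lost without an FRI raises both risks. Counting the latter as infection-free lowers both. Either way, part of the estimate reflects coding and the pattern of loss rather than treatment.

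At stake is the absolute effect, which the article itself expects others to reuse. The same section also means these analyses to show whether method choices influenced the results, and an estimate that moves with dropout coding serves that purpose less well.

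**Working it through.** **Inputs from the protocol article**
- Risks, from the section *Sample size {14}*: "An absolute risk reduction of 12 to 6" per cent, a true difference of 6.0 points.
- Loss, same section: 20%.
- Size, same section: "a sample size of 445 individuals per treatment arm for a total of 890 enrolled patients", with a "two-tailed alpha of 0.05" and 80% power.
- FRI timing, from *Outcomes {12}*: only that diagnoses should peak between 6 weeks and 6 months.

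**Assumed, because the article gives no figure**
- FRI timing: 15% before 6 weeks (1.5 months), 60% from 6 weeks to 6 months, 25% from 6 to 12 months, spread evenly within each interval.
- Loss spread evenly over 12 months and unrelated to FRI.

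**Step 1: the stated sample size.** With mean risk 0.09 and pooled variance:

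n = [1.960 × √(2 × 0.09 × 0.91) + 0.8416 × √(0.12 × 0.88 + 0.06 × 0.94)]² / 0.06² = 355.9, so 356 per arm. 356 / 0.8 = 445. The stated figure is reproduced.

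**Step 2: standard error of the risk difference.** √[(0.12 × 0.88 + 0.06 × 0.94) / 356] = √(0.162 / 356) = 0.0213, or 2.1 points. The 95% CI around 6.0 is about 1.8 to 10.2.

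**Step 3: share of FRIs seen before loss.** Mean FRI time = 0.15 × 0.75 + 0.60 × 3.75 + 0.25 × 9 = 4.61 months. With loss time uniform on 0 to 12 months, the share seen first is 1 − 4.6125 / 12 = 0.616.
- Placebo: 0.12 × 0.6156 = 0.0739 of the patients who leave have an observed FRI.
- Gentamicin: 0.06 × 0.6156 = 0.0369.

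**Step 4: the risk difference under each coding, 20% loss in both arms**

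| Coding | Placebo | Gentamicin | Difference (points) |
|---|---|---|---|
| Lost without FRI counted infection-free | 0.8 × 0.12 + 0.2 × 0.0739 = 0.1108 | 0.8 × 0.06 + 0.2 × 0.0369 = 0.0554 | 5.5 |
| Lost without FRI dropped, early FRIs kept | 0.1108 / (0.8 + 0.2 × 0.0739) = 0.1360 | 0.0554 / (0.8 + 0.2 × 0.0369) = 0.0686 | 6.7 |
| Every lost patient excluded | 0.1200 | 0.0600 | 6.0 |

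A simulation with 2,000,000 patients per arm gave 5.54, 6.74 and, for Kaplan-Meier, 6.00 points.

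**Step 5: cost of the third coding.** Of 445 per arm, 89 leave. Observed FRIs discarded: 89 × 0.0739 = 6.6 on placebo and 89 × 0.0369 = 3.3 on gentamicin, about 10. Observed in total: 445 × 0.1108 + 445 × 0.0554 = 49.3 + 24.6 = 73.9. About 13% of the observed primary events are thrown away.

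**Step 6: sensitivity to the timing assumptions.** With constant hazard, or FRI uniform from 6 weeks to 6 months, and loss either even over the year or all at about 2 weeks, the first coding gives 4.8 to 5.6 points and the second 6.0 to 6.8.

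**Step 7: unequal loss, an assumption without support in the article.** With 30% loss on placebo and 10% on gentamicin, the step 4 formulas give 4.8 and 8.3 points; Kaplan-Meier stays at about 6.0. With 12% risk in both arms, so no effect, they give −0.9 and +2.0 points.

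**The case against.** Several stronger readings are tempting, and the document does not carry them.

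- *The plan ignores follow-up time in the risk difference.* The article says this only of Fisher's exact test. For the risk difference it names a link and does not say how partial follow-up enters. That it cannot enter is an inference from the type of model, though a reasonable one, since person-time is given as the reason for the other link.
- *With 20% loss the estimate is therefore biased.* This does not follow. If loss is unrelated to infection and every lost patient is excluded, the estimate is 6.0. That holds, at the price of discarding FRIs already diagnosed.
- *It conflicts with the primary analysis.* A relative hazard and a risk difference are different summaries. The article discloses that they may disagree, gives only an interval, and leaves the primary test and its alpha untouched.
- *Loss will differ by arm.* Nothing suggests it. The treatment is one intraoperative injection, and participants, care providers and assessors are masked. A telephone FRI screen after missed visits should also limit missing outcomes.
- *The no-imputation rule must give way to multiple imputation or a tipping-point analysis.* That is a general missing-data request, separate from this point, and such sensitivity analyses are commonly left to an analysis plan.

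The comparison also favours Kaplan-Meier, since independent censoring is the condition under which it is unbiased. Loss related to infection would harm it, and the person-time primary analysis as well.

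What remains is narrower: the article does fix a model, and that model suits incomplete follow-up less well than alternatives already within reach.

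**Conclusion.** The point holds as a modest weakness in a supportive analysis. The chosen model makes the absolute effect depend on a coding rule that the article does not state. With equal, non-informative 20% loss and the assumed FRI timing, the two codings that keep observed FRIs move a true 6.0 points to 5.5 or 6.7. That is a shift of about 0.5 to 0.7 points, roughly a fifth to a third of the standard error of 2.1. Over the other timings tried, the shift runs from −1.2 to +0.8 points. The direction of effect does not change. The shift becomes large only if loss differs between arms, which is hypothetical here.

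A reader should not infer that the primary result is at risk or that the plan contradicts itself. The reason to act is that the article gives the risk difference weight beyond this trial, and that the dependence on coding can be avoided.

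**What to change.** In *Statistical methods used for secondary and additional outcomes*, replace the identity-link regression by the 12-month FRI risk difference with a 95% CI, obtained in one of two ways:
- the difference between the two Kaplan-Meier FRI risks at 12 months; or
- the difference between standardised 12-month risks from the primary complementary log-log model.

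Either should use every randomised patient's available follow-up. No P-value is needed, as now. The second option ties the absolute effect to the primary model and removes most of the disclosed inconsistency. The first does not depend on that model's form.

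The cost is slightly more programming, for example a bootstrap or delta-method interval, and no new data. The limitation is that both options still assume non-informative loss, as the primary analysis does.

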### Interim analyses {21b}

Interim analysis will be conducted by the trial statistician and reported to the DSMC when the milestones of 1/3 target enrollment and 2/3 of target enrollment have been met. Statistical evidence of harm at either interim analysis will result in trial discontinuation. In addition, both interm analysis events will evaluate futility using a cutoff of a conditional power to detect 20% as the threshold for either discontinuation of the trial or protocol changes at the discretion of the DSMC.

### Methods for additional analyses (e.g., subgroup analyses) {20b}

We will evaluate the several subgroups of clinical interest for any differential treatment effects of local gentamicin administration. These groups include (i) Gustillo-Anderson classification, (ii) severity of wound contamination (minimal vs moderate vs severe using the OTA open fracture classification for contamination), (iii) time from injury to surgery (< 24 h vs > 24 h), and (iv) type of definitive fixation (external fixation vs intramedullary nailing). This analysis will be reported descriptively and with confidence intervals, but no significance *P*-values will be given. Conclusions based on such subgroups or adjustments will be considered hypothesis-generating and will not form the basis for highlighting in reports or publications.

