#### Intervention description {11a}

A certified unmasked study nurse will prepare 5-ml aqueous gentamicin (16 mg/ml) and 5-ml normal saline solutions. The solutions are prepared in identical syringes labeled with the solution expiration date and either “solution A” or “solution B” according to the masking key before they are stored in a locked study fridge adjacent to the operating theater. The masking key is only accessible to the study nurse. Solutions are stored at 4 °C for up to 48 h, per pharmacist guidelines, and a solution preparation log is maintained to ensure the integrity of the study solutions.

At the conclusion of the index surgical procedure (wound debridement, skeletal stabilization, as appropriate), the surgeon confirms that the wound can be closed primarily. At that point, the patient is randomized using the Research Electronic Data Capture (REDCap) randomization tool. The appropriate study solution is then injected into the closed wound using a 22-gauge needle down to the bone through an anteromedial approach at the level of the fracture site using a sterile technique (Fig. 1).

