#### Relevant concomitant care permitted or prohibited during the trial {11d}

All patients will undergo standard of care treatment for open tibial shaft fractures at MOI regardless of their eligibility for enrollment in the study. This includes several perioperative co-interventions:Systemic antibiotic prophylaxis: All patients will receive a single dose of 1-g IV ceftriaxone as soon as possible after presentation to the hospital.Surgical debridement: All patients will undergo systematic debridement of the traumatic wound with the removal of any devitalized bone and soft tissue. Once the surgeon has deemed appropriate debridement has taken place the wound will be irrigated.Fracture stabilization: Fixation of the fracture will be at the discretion of the treating surgeon. It will be temporizing or definitive using either external fixation (EF) or intramedullary nailing (IMN). External fixation will be with a uniplanar external fixator consisting of a minimum of two Schanz pins proximal to the fracture and two Schanz pins distal to the fracture connected by a single stainless steel bar. Pin care protocol will consist of cleaning the pin sites with methyl alcohol twice daily for the duration of the external fixator placement. Intramedullary nailing will utilize the SIGN intramedullary nail system. An infrapatellar approach will be utilized with two proximal and two distal locking screws placed using an external jig. Intraoperative fluoroscopy will not be used routinely.Wound closure and wound care: The wound will be closed primarily when it is felt safe and feasible to do so by the operating surgeon. The wound will be checked at the 2-week visit, and if dry the dressing will be removed. If it is not, the patient will be instructed to perform additional wound care.Weight bearing protocol: All patients will be advised to be on toe-touch status for the first 6 weeks following surgery. Afterwards, the patient will be instructed to weight bear as permitted by pain.

The study has no prohibited concomitant care. Patients may continue to use any additional medications so long as it is not placed locally around the wound site. If a medication is applied locally to the wound site, it will be recorded as a protocol violation.

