### Data collection and management

#### Plans for assessment and collection of outcomes {18a}

All data collection will be carried out by the 3 research coordinators. The research coordinators have undergone training on the proper employment of all appropriate scales and surveys used in the study.

All patients possessing potentially eligible open tibia fractures will be screened by the program coordinators. Should a patient prove eligible and provide informed consent, basic demographic information, including socioeconomic status, medical and social history, injury characteristics, and estimated pre-injury quality of life, will be collected. Health-related quality of life will be measured using the validated and widely used EuroQol EQ-5D survey [16]. Personal contact information will be obtained along with contact information for at least two close contacts to optimize follow-up. Preoperative orthogonal radiographs and serum creatinine will also be obtained.

The patient will then proceed for operative treatment and definitive fixation at the discretion of the treating surgeon. Wound size measurements (using a centimeter ruler or the handle of a scalpel) will be taken of the maximum dimension of the wound both prior to debridement and after debridement. OTA open fracture classification, Gustillo-Anderson classification, fracture fixation data, and the total time to fixation will be recorded.

Following the intervention, postoperative orthogonal radiographs and serum creatine collected on postoperative day 2 will be obtained. Preoperative radiographs will undergo OTA fracture classification and postoperative radiographs will be measured for any coronal or sagittal angulation by a trained member of the coordinating center. Prior to discharge, the research coordinator will meet with each patient to schedule their follow-up appointments and document any in-hospital complications.

At the 2-week follow-up appointment, serum creatinine and CRP will be drawn. Patients will complete the outcomes assessment surveys for fracture-related infection, current pain level, unplanned fracture-related reoperation, and other adverse events [17]. At the 6-week follow-up, only the CRP will be drawn and the patient will again complete all the same surveys done at the 2-week visit.

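### The fixation subgroup uses definitive fixation, which for patients first given temporizing fixation is settled after randomisation, so its contrast can be distorted

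*Protocol article*

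**What the plan says.** Five statements in the protocol article bear on this point.

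- **Subgroups ({20b}).** The fourth subgroup is "iv) type of definitive fixation (external fixation vs intramedullary nailing".
- **Concomitant care ({11d}).** "Fixation of the fracture will be at the discretion of the treating surgeon". The next sentence adds: "It will be temporizing or definitive using either external fixation (EF) or intramedullary nailing (IMN".
- **Intervention description ({11a}).** "At the conclusion of the index surgical procedure (wound debridement, skeletal stabilization, as appropriate), the surgeon confirms that the wound can be closed primarily". Then: "At that point, the patient is randomized using the Research Electronic Data Capture (REDCap) randomization tool".
- **Data collection ({18a}).** Before it turns to what follows the intervention, this section says: "The patient will then proceed for operative treatment and definitive fixation at the discretion of the treating surgeon". It lists fracture fixation data among the items recorded at this stage.
- **Secondary and additional outcomes.** The variables introduced as baseline covariates for sensitivity analyses end with "time from injury to first debridement, and method of fixation". The word definitive is not used there.

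On the standing of subgroup results, {20b} says: "Conclusions based on such subgroups or adjustments will be considered hypothesis-generating". They are to be shown with confidence intervals and without P-values.

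**The concern.** A subgroup comparison keeps the protection of randomisation only if membership is fixed before allocation, or at least cannot be affected by what happens afterwards. Under {11d} and {11a}, a patient can be randomised and injected while holding a temporizing device. The definitive device is then chosen later, at the surgeon's discretion, while FRI is being assessed from the 2-week visit onward. If an early infection makes conversion to a nail less likely, infected patients collect in the external-fixation stratum and leave the nail stratum. If gentamicin prevents early infections, the two arms are also sorted differently. An apparent difference in benefit between fixation types could then arise where none exists.

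The article is not consistent about the variable either. The data-collection section reads as if definitive fixation always comes before the injection, which does not fit the temporizing option in {11d}. The covariate list treats fixation as a baseline quantity. No stated rule says how a temporised patient is classified.

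**Working it through.** **Timing, from the text.** Index operation, with temporizing or definitive fixation ({11d}) → primary closure confirmed and patient randomised ({11a}) → injection → follow-up for FRI from 2 weeks. For patients with definitive fixation at the index operation, the subgroup is known before allocation. For temporised patients it is not.

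**The plan's own figure.** The article gives no figure for this subgroup. Its sample size reproduces from 12% vs 6%, two-sided alpha 0.05 and power 80%:

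n = [1.96·√(2·0.09·0.91) + 0.842·√(0.12·0.88 + 0.06·0.94)]² / 0.06² ≈ 356 per arm; 356/0.80 = 445 per arm, 890 in total.

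Nothing in this point changes that.

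**Illustration.** From the article: planning risks p = 0.12 (control) and p = 0.06 (gentamicin), used here for every patient whatever the device. Assumed, because the article is silent:

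- the shares given definitive external fixation at the index operation (e), temporised (t) and nailed at the index operation (n);
- 25% of FRIs in each arm occur before conversion;
- every temporised patient infected before conversion stays in external fixation, and every other temporised patient is nailed.

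Formulas, by arm:

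- Risk, external = (e·p + 0.25·t·p) / (e + 0.25·t·p)
- Risk, nail = (n·p + 0.75·t·p) / (n + t·(1 − 0.25·p))
- Relative hazard = ln(1 − gentamicin risk) / ln(1 − control risk), the scale of the complementary log–log primary model

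Scenario A (e, t, n = 0.40, 0.30, 0.30):

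- External, control: 0.0570/0.4090 = 13.9%; gentamicin: 0.0285/0.4045 = 7.0%
- Nail, control: 0.0630/0.5910 = 10.7%; gentamicin: 0.0315/0.5955 = 5.3%

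Scenario B (e, t, n = 0.10, 0.60, 0.30):

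- External, control: 0.0300/0.1180 = 25.4%; gentamicin: 0.0150/0.1090 = 13.8%
- Nail, control: 0.0900/0.8820 = 10.2%; gentamicin: 0.0450/0.8910 = 5.1%

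| | Risk difference, external vs nail (points) | Risk ratio, external vs nail | Relative hazard, external vs nail |
|---|---|---|---|
| Truth | 6.0 vs 6.0 | 0.50 vs 0.50 | 0.484 vs 0.484 |
| Scenario A | 6.9 vs 5.4 | 0.506 vs 0.496 | 0.487 vs 0.482 |
| Scenario B | 11.7 vs 5.2 | 0.541 vs 0.495 | 0.505 vs 0.482 |

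**Softer sorting, and an effect mainly on early FRI.** A second set of assumptions:

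- 10–50% of all patients are temporised in an external fixator;
- 10–30% of the others have definitive external fixation;
- 90% of those infected before conversion stay in external fixation, and 90% of the rest are nailed.

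Results, with the overall risk ratio still 0.50 for everyone:

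- Same risk ratio for early and late FRI, with 25–50% of control FRIs early: risk difference 6.3–13.0 (external) vs 4.7–5.9 (nail) points; risk ratio 0.50–0.55 vs 0.49–0.50.
- Early risk ratio 0.3 and late 0.7, with half of control FRIs early: risk difference 7.0–16.7 vs 4.1–5.7 points; risk ratio 0.42–0.48 vs 0.51–0.56.

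**Null checks.** With nobody temporised, or with conversion unrelated to infection, both strata return 0.50 and 6.0 points. Defining the strata by fixation at the end of the index operation also returns the truth in both.

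**The case against.** The strongest reply has four parts.

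1. **The text can be read as pre-randomisation.** The data-collection section places definitive fixation before the intervention, and the schedule of events shows no conversion procedure. This is real evidence for that reading. It cannot be squared with the temporizing option in {11d}, however, so it leaves a contradiction to resolve.

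2. **The size rests on assumptions and on the scale.** This stands. Every fixation share, the early-FRI fraction and the link from infection to device are assumed, and scenario B is close to a worst case. On the relative-hazard scale scenario A shows almost nothing, and scenario B shows a small shift in the opposite direction, with external fixation appearing to benefit slightly less. Much of the risk-difference gap reflects the higher control risk that sorting creates in the external stratum. Against that, {20b} does not name the subgroup scale, and the article elsewhere plans an overall risk difference and calls it important for interpretation.

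3. **The results are exploratory.** No P-values are given and the findings are not to be highlighted. This limits the harm. It guards against over-reading chance findings but does not remove a systematic bias, which a larger sample would not cure.

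4. **The covariate wording may be condensed.** The gap between method of fixation and definitive fixation is weak evidence alone, since detailed definitions may sit in an analysis plan that is not shown. It matters only because a variable called baseline should be fixed at baseline.

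A reader might infer that these subgroup effects will be distorted, by a known amount, or that the main result is at risk. The article supports none of these. It does not say that anyone will in fact be temporised, when conversion would happen, or that infection would influence it. That last step is an inference from surgeon discretion and the timing of FRI assessment.

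**Conclusion.** The point holds as one of definition and timing. As written, the fourth subgroup can be set after randomisation for temporised patients and can depend on early FRI, so its contrast can be distorted. The article also contradicts itself on whether definitive fixation always precedes the injection.

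The size cannot be determined from the article. It runs from zero up to a risk-difference gap of about 6.5 points (11.7 − 5.2) in the more extreme of scenarios A and B, where the relative hazards differ by only about 0.02 (0.505 − 0.482). Ratio-scale distortion becomes material only under the further assumption that gentamicin acts mainly on early infection. With the primary analysis and the 890 untouched and the subgroup labelled hypothesis-generating, the severity is minor.

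**What to change.** - Define the fourth subgroup by the fixation in place at the end of the index operation, before randomisation: nail vs external fixator. If the surgeon's intent (temporizing or definitive) is recorded at that time, split the external fixators by it.
- Use the same definition for the fixation covariate in the sensitivity analyses.
- Report eventual definitive fixation by arm descriptively only.
- Reconcile the data-collection section ({18a}) with the concomitant-care section ({11d}) on whether fixation at the index operation may be temporizing.

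The cost is a few words in three sections. Fixation data are already collected around the index operation; whether intent is recorded is not stated. This changes an analysis variable and no surgeon's choice of device. The one real downside is that the subgroup then answers a question about index fixation, not about eventual fixation. The change is best made before any unmasked results are seen.
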